### Dietary intake

3-day food records (2 weekdays, 1 weekend day), a validated tool for diet analysis, were completed [36,44]. Responses were verified by an RD on the research team (blinded to study allocation) and analyzed for micro- and macronutrient intake (e.g. calcium, vitamin D, phosphorus, carbohydrates, protein and caffeine) using Food Processor® (Canadian Nutrient File®).

### Weight-bearing physical activity

Analysis of the frequency/duration/effects of weight-bearing physical activity utilizing a record adapted from a validated physical activity questionnaire [34,42].

### Sunlight exposure questionnaire/seasonal affects

Participants completed a validated questionnaire for vitamin D synthesis potential according to sun exposure behaviours [43]. This questionnaire was completed to help account for seasonal variations and the impact this may have on vitamin D synthesis.

### Safety variables and analysis

Safety analysis included an evaluation of the literature and the potential for the following: 1) hypercalcemia [27,41,45] 2) signs and symptoms of acute toxicity (rare) including evidence “anorexia, nausea, vomiting, fatigue, confusion, headache, weakness, renal impairment, arrhythmias, hypertension, calcification of soft tissue and hyperphosphatemia” [41].

Adverse events with vitamin D_3_ supplementation at these dosing levels (40,000 IU/month or 2000 IU/D) have not been routinely reported in the literature [11,45-47]. Supplementation with active vitamin D analogues may be useful for individuals with severely diminished renal function and capacity for active hydroxylation, and is primarily used to treat severe hyperparathyroidism. However, providing already active vitamin D results in bypassing the homeostatic controls that are in place to prevent vitamin D toxicity (e.g. reducing 25-hydroxylation and increasing catabolism and excretion of 25(OH)D via bile), which in turn can increase risk for vitamin D toxicity [23,46]. Serum phosphate (>2.0 mmol/L), calcium-phosphorous product (CaP; >4.4 mmol^2^/L^2^) and magnesium (>1.0 mmol/L) are all monitored as part of routine clinical care for variation from healthy ranges [41].

A data safety monitoring board (DSMB) was included within the study design. All adverse events (AE) were documented. AEs were identified as related to the study protocol (e.g. anything directly related to our vitamin D supplementation intervention, blood collection or other examinations in the study protocol) or not related to the study protocol. Serious adverse events (SAEs) were defined as significant health/safety issues (e.g. acute renal failure, death). The responsible physician (PS), University HREB, and DSMB were notified of all AE/SAE. No SAEs due to study protocol occurred in this study.

#### Concomitant medication

Patients were asked to continue taking their normal medications as advised by their physician, e.g. insulin, oral hypoglycaemic agents, anti-hypertensives, statins, diuretics, phosphate binders, potassium lowering agents, anemia treatment, Replavite, and/or proton-pump inhibitors. Concomitant medications were reviewed at each visit to ensure excluded medications were not prescribed in the interim. Any patients medically requiring a concomitant medication that was contraindicated were released from the study. Participants were asked to discontinue all vitamin/mineral supplements containing calcium and/or vitamin D unless prescribed for therapeutic treatment (such as calcium carbonate-containing antacids for treatment of hyperphosphatemia). Those on active vitamin D treatment (with other vitamin D metabolites) were excluded from the study.

#### Rescue medication & risk management

Serum phosphate (>2.0 mmol/L), CaP product (>4.4 mmol^2^/L^2^) and magnesium (>1.0 mmol/L) were monitored throughout the study [48]. Vitamin D toxicity was addressed in the following ways: a) discontinuation of vitamin D_3_ supplement and b) notification to the Qualified Investigator (PS) and other members of the health care team in NARP/DNPC.

The following were standard responses to vitamin D toxicity in our population: 1) Serum and urine electrolytes, renal function, electrocardiogram, and fluid balance monitoring and maintenance [38]. 2) If necessary, additional measures may have been taken to enhance excretion/metabolism of the vitamin D including: IV administration of furosemide; corticosteroid, bisphosphonate or calcitonin therapy; hemo- or peritoneal dialysis [43]. If hypersensitivity to vitamin D_3_ occurred which included anaphylaxis, then appropriate treatment with epinephrine and ventilation would have been provided as needed.

Adverse events were reported immediately to the responsible physician (PS) or the on-call endocrinologist/nephrologist was notified as per standard clinical care. Participants were taken to the University of Alberta Hospital, AHS if requiring immediate medical treatment.

#### Premature withdrawal

Participants were able to voluntarily withdraw from the trial at any time without any negative consequences to their clinical care. Any and all reasons for participant drop out were documented. Any individual demonstrating clinical signs and symptoms of vitamin D toxicity and/or an SAE related to the study protocol resulted in: 1) vitamin D_3_ supplementation discontinued, 2) responsible physician (PS) notified so the patient received treatment for toxicity (as above), 3) notification of the DSMB and Health Canada, and 4) patient participation in the study was discontinued. New medical diagnosis arising precluding the ability to continue in the study was an additional reason for premature withdrawal. This was assessed by the qualified investigator (PS).

### Statistical analysis

Data analysis was performed on an intention-to treat basis as well as a per-protocol basis. Analyses were performed using Microsoft Excel 2010 and Statistical Analysis Software (SAS; version 9.3 SAS Institute, Cary, NC, USA). Statistical significance was determined at p < 0.05. Continuous variables were expressed as mean, median, ranges, and standard error (SE) or standard deviation (SD). The differences between dosing type (daily vs. monthly) over the intervention period were assessed by repeated measures analysis of variance, followed by a post-hoc pair-wise t-test with Bonferroni corrections to assess for within and between group comparisons. Potential risk factors for the development of vitamin D insufficiency (serum 25(OH)D <75 nmol/L) and poor bone health (T-scores < −2 SD) in adults with diabetic nephropathy include bone turnover, vitamin D intake, vitamin D status (serum levels of 25(OH)D and 1,25(OH)_2_D), age, gender, ethnicity, severity of kidney disease, diabetic management/control, exposure to sunlight, level of activity, and psychosocial and lifestyle factors.

Continuous and categorical variables (e.g. 25(OH)D, lab parameters, BMD T-scores, adherence scores) were quantitatively analyzed, and open-ended questions regarding participants’ perceived facilitators and barriers were categorized into key themes. Bivariate and univariate analysis were done to assess the potential effect of these variables on vitamin D status and bone health (bone turnover markers).Variables shown to be associated with a poor vitamin D status were assessed using multivariate logistic regression models to determine risk for development of vitamin D deficiency and poor bone health. Regression analysis was also conducted to assess correlation between biochemical parameters (PTH, 25(OH)D, 1,25(OH)_2_D, calcium, phosphorus, magnesium, albumin, eGFR, RBG) and bone turnover markers. Analysis of variance was performed to assess for significant differences in vitamin D status and bone turnover markers over the intervention period in both groups. Regression analysis was performed with serum 25(OH)D and plasma PTH as categorical variables; e.g. 25(OH)D sorted by greater/less than 75 nmol/L and plasma PTH sorted by greater/less than 7.15 pmol/L, the optimal concentrations for bone health [5,26]. Where necessary, vitamin D was adjusted for potential confounding variables (e.g. age, gender, ethnicity, disease severity) using an analysis of co-variance. When adherence to daily vitamin D dosing regimen was greater or less than 69%, the variation in compliance was also accounted for in an analysis of co-variance. For variables demonstrating skewed distributions a logarithmic transformation was used to normalize the data.

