## Background

Suboptimal vitamin D status (25(OH)D <75 nmol/L) is associated with the development and progression of both diabetes and chronic kidney disease (CKD) [1]. Within the general North American population 16-52% have suboptimal vitamin D status; the prevalence of vitamin D insufficiency increases to 86% in the diabetic population and those with concurrent kidney disease are 1.78-fold more likely to be vitamin D deficient [2-4]. Patients living in northern communities are at particular risk for vitamin D insufficiency due to limited sunlight exposure, further increasing their risk for low bone mineral density (BMD) and fragility fractures [3,5-10]. Recent evidence indicates that up to 40-90% of patients with stage 3–4 CKD have insufficient/deficient vitamin D status [2,5,11,12]. By the time CKD patients reach dialysis, approximately 75% have metabolic bone disease [13].

Unlike other nutrients, recommendations for vitamin D are not based on food sources as there are very few dietary options available (e.g. fish, liver and fortified dairy products), but rather are designed to compensate for a deficiency of sunlight [14]. This places the individual living in northern climates at particular risk for inadequate vitamin D status, especially in the winter months when sunlight exposure is unlikely to contribute to overall vitamin D status. Most evidence suggests that when vitamin D requirements are met, it is with a combination of dietary vitamin D and a supplement [15-22]. Patients with diabetic nephropathy are at increased risk for poor dietary intake of vitamin D due to restrictions on vitamin D rich foods/beverages (e.g. dairy based products) as these products also have a high carbohydrate, phosphorus and/or potassium content. It is unknown what level of vitamin D supplementation will ameliorate or improve suboptimal vitamin D status in patients with diabetic nephropathy or contribute to improved bone health, particularly for those living in northern climates [5,7,10]. A recent study in patients with stage 3–4 CKD demonstrated that daily oral supplementation of vitamin D_3_ (1,000 IU/d) for three months resulted in a mean increase in serum 25(OH)D of 25 nmol/L (40 ± 15 nmol/L pre- vs. 68 ± 25 nmol/L post-supplementation); a significantly lower level of 25(OH)D than is thought to optimize bone health (>100 nmol/L) [12,23-25].

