### Sample size

This sample size (n = 120) was based on the ability to detect a mean difference of 25–50 nmol/L in serum 25(OH)D from baseline levels after 6 months of vitamin D_3_ supplementation in each group (α = 0.05 and β = 0.8) with an additional 15% to account for potential subject attrition [5,8]. Recent evidence has shown that a mean increase of 25 nmol/L in 25(OH)D with 1,000 IU/day supplemental vitamin D_3_ was insufficient to promote 25(OH)D in excess of 100 nmol/L – the level of 25(OH)D that has been associated with having a beneficial impact on markers of bone health [5,7,23]. Therefore, we chose this specific vitamin D_3_ dose to ensure serum 25(OH)D would increase by 25–50 nmol/L.

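### The daily-versus-monthly comparison has no stated baseline-adjusted contrast and shares one Bonferroni correction with the within-arm tests

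*Protocol article*

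**What the plan says.** In the protocol article, Statistical analysis, differences between dosing types over the intervention period are assessed by "repeated measures analysis of variance, followed by a post-hoc pair-wise t-test with Bonferroni corrections to assess for within and between group comparisons". The general threshold is "Statistical significance was determined at p < 0.05". The section does not say whether the arm effect, the arm-by-time term or a 6-month difference is decisive, nor how many tests share the correction.

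On covariates the same section says: "Where necessary, vitamin D was adjusted for potential confounding variables (e.g. age, gender, ethnicity, disease severity) using an analysis of co-variance". Baseline 25(OH)D is not among the examples.

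25(OH)D is measured at baseline, 3 and 6 months (Data collection; Laboratory investigations), with 60 patients per arm (Study design). The Sample size section aims to detect "a mean difference of 25–50 nmol/L in serum 25(OH)D from baseline levels after 6 months of vitamin D_3_ supplementation in each group", with "α = 0.05 and β = 0.8) with an additional 15% to account for potential subject attrition".

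Data are to be analysed both by intention to treat and per protocol. Under Concomitant medication, "Any patients medically requiring a concomitant medication that was contraindicated were released from the study". Under Premature withdrawal, for toxicity or a related serious adverse event, "patient participation in the study was discontinued"; a new diagnosis that rules out continuing is a further reason to withdraw.

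**The concern.** Daily versus monthly is the only randomised question in the trial, and the stated method fixes it badly in three respects.

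- **Baseline.** With baseline as one of three time levels, the answer depends on which term is read. A group main effect averages in a visit at which neither arm has been treated. A post-hoc t-test at 6 months uses unadjusted values. Only the arm-by-time term brings baseline in, through changes.
- **Shared correction.** Before/after tests within each arm and between-arm tests sit under one Bonferroni correction. The within-arm tests therefore use up error rate that the randomised comparison could have kept.
- **Open covariates.** Adjustment as needed, with no stated criterion, leaves room to choose covariates after the results are known.

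At stake is precision on the randomised comparison, from a baseline measurement that is already in hand. There is also a tension in the text: an intention-to-treat statement stands beside rules that end participation, not only supplementation, so outcomes after that point will be missing.

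**Working it through.** **The plan's own figure.** n = 120 cannot be reproduced, because no SD is given for it. Sixty per arm with 15% attrition leaves 60 × 0.85 = 51 evaluable (or 60/1.15 ≈ 52). I use 51.

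**Inputs**
- SD of 25(OH)D: assumed 25 nmol/L. The only SDs in the document are in the Background, from a cited CKD study at another dose: "40 ± 15 nmol/L pre- vs. 68 ± 25 nmol/L post-supplementation".
- Power 80%: the Sample size section prints this value as β, evidently meaning power.
- Level: two-sided 0.05 (sidedness assumed).
- Correlation ρ between baseline and 6 months: not given; 0.3, 0.5 and 0.7 assumed.
- Equal SDs before and after: assumed, then relaxed.

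**1. Raw 6-month test at 0.05.** Standard error = 25 × √(2/51) = 4.95. The normal approximation gives (1.960 + 0.842) × 4.95 = 13.9; the noncentral t gives **14.0 nmol/L**. This scales with the SD: 14.0 × 15/25 = 8.4 at SD 15, and 14.0 × 35/25 = 19.6 at SD 35.

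**2. Handling of baseline.** In units of the outcome variance, the raw value has variance 1, the change score 2(1 − ρ) and ANCOVA 1 − ρ². Multiplying 14.0 by the square root gives the detectable difference. The last column is 2(1 − ρ)/(1 − ρ²) = 2/(1 + ρ).

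| ρ | raw | change score | ANCOVA | patients needed, change score ÷ ANCOVA |
|---|---|---|---|---|
| 0.3 | 14.0 | 16.6 | 13.4 | 1.54 |
| 0.5 | 14.0 | 14.0 | 12.1 | 1.33 |
| 0.7 | 14.0 | 10.8 | 10.0 | 1.18 |

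**3. Unequal SDs.** With SDs of 15 before and 25 after, the SD of change is √(15² + 25² − 2ρ·15·25) = 25.0, 21.8 and 18.0. The ANCOVA residual SD is 25√(1 − ρ²) = 23.8, 21.7 and 17.9. The patient ratio, change score to ANCOVA, is then only (25.0/23.85)² = 1.10, (21.79/21.65)² = 1.01 and (18.03/17.85)² = 1.02. The gain over the raw test is the same as in step 2.

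**4. Group main effect.** If the arms differ by δ at both 3 and 6 months and by 0 at baseline, the main effect estimates (0 + δ + δ)/3 = 2δ/3. A three-visit mean also has a smaller variance, so this is a dilution of the estimate and not by itself a measure of lost power.

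**5. Bonferroni.** The family is not stated, so I take three assumed sizes: 3 (between-arm tests at three visits), 9 (those plus 2 arms × 3 within-arm pairs) and 15 (all pairs of 6 cell means). The power column uses the normal approximation.

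| family | per-test level | detectable, raw (nmol/L) | power of a contrast with 80% at 0.05 |
|---|---|---|---|
| 1 | 0.05 | 14.0 | 80% |
| 3 | 0.0167 | 16.3 | 66% |
| 9 | 0.0056 | 18.2 | 51% |
| 15 | 0.0033 | 19.1 | 45% |

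**6. Within-arm tests.** With 51 patients and an assumed SD of change of 25, power for a 25 nmol/L change exceeds 99.9%. Making these tests secondary costs little.

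**The case against.** The case for the plan is substantial, and several stronger readings fail against it.

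- **Baseline is not ignored.** With baseline as a time level, the natural test is arm-by-time, which compares changes. This stands. What remains is that the section does not say this term decides, and that under equal SDs it is less efficient than ANCOVA. With the Background's unequal SDs the efficiency gap nearly closes, though the gain over a raw 6-month t-test does not.
- **The covariate list is only illustrative.** It does not exclude baseline 25(OH)D. True, but it does not commit to it either, and the criterion for adjusting is open.
- **A reader might infer that the between-arm test falls below its planned α.** The Sample size section sets 0.05 for change within each group, so no between-arm α was planned. The ANOVA itself is judged at 0.05, and the Bonferroni step errs on the cautious side.
- **A reader might take nine tests as the least the family could hold.** No family is stated and it could be smaller, so 3, 9 and 15 are assumptions.
- **A reader might combine the two penalties**, (18.2/12.1)² ≈ 2.3 times the patients. That sets an assumed unfavourable reading of the plan against the favourable alternative and is not a fair measure.
- **A reader might conclude that intention to treat was not achieved.** The document does not show this. The number withdrawn is unknown; Safety variables and analysis reports no serious adverse event due to the protocol; a likelihood-based fit in SAS would keep partial data; and missing-data handling may sit in a document not shown. Ending participation creates missing outcomes, which is a tension to resolve and not proof of a complete-case analysis.

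**Conclusion.** The concern holds in a limited form. The stated method does not commit to a baseline-adjusted between-arm contrast, and it places the randomised comparison in the same Bonferroni correction as the within-arm tests.

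Against a raw 6-month test, baseline adjustment lowers the detectable difference from 14.0 nmol/L by 0.6 to 4.0 nmol/L across correlations 0.3 to 0.7. Against a change score it saves between about a third of the patients (1 − 1/1.54) and about 15% (1 − 1/1.18) if the SDs are equal, and much less if they are not. The Bonferroni cost ranges from 2.3 to 5.1 nmol/L for assumed families of 3 to 15 tests. All of this rests on an assumed SD of 25 and 51 evaluable per arm.

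This is a gain in precision and clarity at almost no cost, not an error that invalidates the analysis. On intention to treat, the document supports only a request to reconcile the passages.

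**What to change.** - Name the between-arm difference in 6-month 25(OH)D as the primary contrast, tested at two-sided 0.05 and kept outside the Bonferroni family of within-arm tests. 1,25(OH)₂D also appears under Primary outcome variables, so its rank should be stated; 25(OH)D is the variable on which the sample size rests.
- Estimate the contrast from a likelihood-based mixed model on the 3- and 6-month values, with baseline 25(OH)D as covariate, using all randomised patients with any post-baseline value.
- Replace adjustment as needed with a covariate list fixed in advance.
- Keep the 3-month data of patients who left before 6 months.
- Reconcile the intention-to-treat statement in Statistical analysis with the rules in Concomitant medication and Premature withdrawal that end participation, stating who is in the analysis and what is assumed about missing outcomes. This is a matter of analysis wording and implies no view on the clinical rules.

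The cost is some rewording and minor reprogramming; the model needs no data beyond the scheduled visits. The price is that the within-arm tests become secondary.

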## Methods

### Study design

The study design was a randomized, controlled, open-label trial comparing the effectiveness of two vitamin D_3_ dosing strategies (monthly vs. daily) on vitamin D status and markers of bone health in adults with diabetes and nephropathy over a 6 month period. Patients were randomized to one of the two vitamin D_3_ supplementation strategies in blocks of 30 using a random number generator (http://www.randomizer.org) by one graduate student (SJ): once monthly (40,000 IU/m; n = 60) or once daily (2,000 IU/d; n = 60) for six months. All members of the research team (with the exception the graduate students (SJ/MH)) were blinded to study allocation. Both vitamin D supplements contain vitamin D_3_ (cholecalciferol) in gel capsule form; Jamieson Natural Sources® Vitamin D 1,000 IU Soft gel (NPN 80017530), and EURO-Pharm International Canada Inc.® EURO D 10,000 IU (DIN 02253178). The two dosing regimens were: 2 capsules of 1,000 IU vitamin D daily (total dose = 2,000 IU/d), or 4 capsules of 10,000 IU vitamin D at the end of each month (total dose = 40,000 IU/m). The daily dose was selected based on results from findings that showed that patients with diabetes with stage 3–4 CKD in Northern Alberta where supplementation with 1000 IU/D vitamin D3 resulted in serum increases of 25(OH) vitamin D less than 25 mmol/L [5,7]. A monthly dose of 40,000 IU/m vitamin D_3_ was chosen to achieve equivalent supplementation to daily dosing assuming an adherence rate of 69%, and with the goal of obtaining a serum 25(OH)D concentration of 100 nmol/L [27,32].

This study was approved by the Human Research Ethics Board at the University of Alberta (File Number: Pro00022639), has received a “No Objection Letter” from Health Canada (Control File Number 148625), and is a registered clinical trial (NCT01476501). The study was monitored by a Drug and Safety Monitoring Board (DSMB) with annual safety reports submitted as per Health Canada protocol. Reporting of study results will be according to the CONSORT (Consolidated Standards of Reporting Trials) Guidelines [33].

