### Exclusion criteria

1) Patients with co-morbid conditions known to affect vitamin D metabolism including gastrointestinal, liver, rheumatoid or bone disorders (e.g. hyperthyroidism, untreated celiac disease, cancer, Paget’s disease, sarcoidosis, malabsorption, etc.). Individuals with severe, permanent vision impairment will be excluded as this will preclude them from reading supplement labels accurately and safely. Pregnant women will be excluded as Dual-energy X-ray Absorptiometry (DXA) scans are not recommended during pregnancy. Patients weighing >136 kg will be excluded as the DXA table cannot accommodate this weight.

2) Patients on drug therapy known to interfere with vitamin D (e.g. oral glucocorticoids, cholestyramine, colestipol, mineral oil, Orlistat, digoxin).

3) Patients on other forms of active D metabolites (e.g. calcitriol, vitamin D2).

4) Patients with stage 5 CKD (GFR <15 mL/min/1.73 m^2^), receiving dialysis or on a kidney transplant list.

5) Patients with pre-existing hypercalcemia (>2.75 mmol/L), hyperphosphatemia (>2.0 mmol/L), severe secondary hyperparathyroidism (PTH >66 pmol/L), and serum 25(OH)D >200 nmol/L.

6) Patients with serum 25(OH)D <37.5 nmol/L at time of screening to control for correction of vitamin D deficiency [5].

7) Patients undergoing strict heavy exercise for weight control and/or those who used sunscreen lotion on a regular basis.

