### Data collection

Assessment of vitamin D status, bone health and lifestyle factors (diet, physical activity, sunlight exposure, QoL) were performed during study visits at the Clinical Research Unit (CRU) at the University of Alberta at baseline, 3 and 6 months post study enrolment between January 2012 and June 2014. Participants were given a 3 month supply of their respective vitamin D_3_ supplementation strategy at baseline and again at the 3 month study visit. They were asked to return their vitamin D_3_ vials/pill containers to the study investigators at the 3 and 6 month study visits. At baseline, information related to patient demographics and anthropometrics was collected. This included age, gender, ethnicity, medications/supplement use, insulin regimen, height, weight (Health O-Meter Professional model 597KL, Pelstar LLC, Alsip, IL, USA) and BMI. Changes in these variables between appointments were documented (e.g. medications, height, weight). Bone mineral density (BMD) was measured at baseline using Dual-energy X-ray Absorptiometry (DXA); a validated tool to assess BMD (General Electric LUNAR Prodigy, version 10.5, Madison, WI, USA). Whole body scans as well as site specific scans of the lumbar spine (L1-L4) and left total hip (including femoral neck) were conducted. The precision error, expressed as a percentage coefficient of variation (%CV), for the Lunar DXA located in the CRU are as follows: whole body BMD 0.7%, lumbar spine 0.9% and total hip 1.2%.

Lifestyle factors were assessed at baseline, 3 and 6 months using validated tools [35-41]. These include: 1) 3-day food record to assess vitamin D and calcium intake and other dietary factors known to influence vitamin D and bone health (phosphorus, carbohydrates, protein, caffeine). Dietary intake was analyzed using the Food Processor Database (Food Processor SQL, v.10.8, ESHA Research, Salem, Oregon, USA); 2) Weight-bearing physical activity records; 3) Sunlight exposure questionnaires; 4) Health related QoL (SF-36) questionnaires (http://www.qualitymetric.com Liscence Number QM019185 OPTUMInsight^TDM^); and 5) Adherence and acceptance surveys [34-38,42-44]. Adherence to vitamin D_3_ supplementation was also assessed by pill counts of returned vitamin bottles at 3 and 6 months.

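### Baseline weight and BMI are collected under fixed-IU dosing but have no named role in the 25(OH)D adjustment or the risk-factor models: a minor, free improvement

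*Protocol article*

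**What the plan says.** All places are in the protocol article.

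- **Data collection.** The baseline record includes "height, weight (Health O-Meter Professional model 597KL, Pelstar LLC, Alsip, IL, USA) and BMI". Later visits update it: "Changes in these variables between appointments were documented (e.g. medications, height, weight".
- **Study design.** Doses are fixed: "2 capsules of 1,000 IU vitamin D daily (total dose = 2,000 IU/d), or 4 capsules of 10,000 IU vitamin D" once a month. Nothing scales them to body size.
- **Exclusion criteria.** The only limit on weight is a scanner limit: "Patients weighing >136 kg will be excluded as the DXA table cannot accommodate this weight". No lower limit is given.
- **Statistical analysis, arm comparison.** Daily and monthly dosing are compared by repeated measures analysis of variance, with no covariate named.
- **Statistical analysis, risk factors.** The candidates for vitamin D insufficiency and poor bone health are bone turnover, vitamin D intake, vitamin D status and "age, gender, ethnicity, severity of kidney disease, diabetic management/control, exposure to sunlight, level of activity, and psychosocial and lifestyle factors". Variables found to be associated with poor vitamin D status go on to multivariable logistic regression.
- **Statistical analysis, covariance adjustment.** The article states that "vitamin D was adjusted for potential confounding variables (e.g. age, gender, ethnicity, disease severity) using an analysis of co-variance". The sentence opens with a condition: "Where necessary, vitamin D was adjusted for potential confounding variables". No rule says when adjustment is necessary.

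**The concern.** With a fixed dose, intake per kilogram falls as body weight rises, so body size is a plausible source of variation between patients in the 25(OH)D response. The variable is already in the database, yet no analysis in the article uses it by name.

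Two different things are at stake:

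1. **The arm comparison.** A baseline covariate that predicts the outcome reduces residual variance. Not using it costs precision.
2. **The risk-factor models.** These are observational. If body size is related both to a listed factor and to 25(OH)D or the T-score, and is never screened, its effect may be attributed to the listed factor.

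In addition, adjusting only when it seems necessary, without a criterion, leaves the choice of covariates open until results are known.

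**Working it through.** **Stated figures.** The plan gives no figure on this point to reproduce. The sample size of 120 (60 per arm) is not in dispute here.

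**Step 1: how far dose per kilogram can vary.** Inputs: 2,000 IU/d (Study design), the 136 kg limit (Exclusion criteria), and a low weight of 50 kg, which is an assumption.

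- At 136 kg: 2,000 / 136 = 14.7 IU/kg/d
- At 50 kg: 2,000 / 50 = 40 IU/kg/d
- Ratio: 136 / 50 = 2.7

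If the low end is assumed to be 70 kg, the ratio is 136 / 70 = 1.9. This compares extremes. It makes body size a plausible covariate but does not measure its effect on serum 25(OH)D.

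**Step 2: precision in the randomised comparison.** Inputs:

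- evaluable patients: 60 × 0.85 = 51 per arm, 102 in total (60 per arm and 15% attrition, from Study design and Sample size);
- SD: 25 nmol/L, the post-supplementation value cited in Background, assumed to apply here;
- correlation r of baseline BMI with the 25(OH)D outcome: not in the document, assumed 0.2 to 0.4.

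Formulas: SE multiplier = √(1 − r²); 95% half-width = 1.96 × 25 × √(2/51) × √(1 − r²); equivalent total n = 102 / (1 − r²).

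| r (assumed) | r² | SE multiplier | 95% half-width, nmol/L | Equivalent extra patients | Power, assumed 14 nmol/L difference |
|---|---|---|---|---|---|
| no adjustment | 0 | 1 | 9.70 | 0 | 80.7% |
| 0.2 | 0.04 | 0.980 | 9.51 | 4 | 82.3% |
| 0.3 | 0.09 | 0.954 | 9.26 | 10 | 84.2% |
| 0.4 | 0.16 | 0.917 | 8.89 | 19 | 87.0% |

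The standard error falls by about 2% (r = 0.2) to 8% (r = 0.4). At r = 0.1 the gain is 0.5%, and at r = 0.5 it is 13%. For a between-arm difference of 25 nmol/L at this SD, unadjusted power is already 99.9%.

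**Step 3: bias in the randomised comparison.** Allocation is random, so body size is balanced between arms in expectation. Leaving it out does not bias the daily versus monthly effect.

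**Step 4: the risk-factor models.** Randomisation gives no protection here. In a linear model that omits BMI, the coefficient of a listed factor such as activity is shifted by (effect of BMI on the outcome) × (slope of BMI on that factor, given the others). The shift is zero only if one of the two terms is zero. The document gives neither, so its size cannot be computed.

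Whether the candidate list already covers BMI turns on its closing category of lifestyle factors. Data collection explains lifestyle as diet, physical activity, sun exposure and quality of life, and reports anthropometrics separately. So BMI is not clearly covered. A variable that is not screened cannot reach the multivariable model.

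**The case against.** **The lists are open.** This is the strongest objection, and much of it stands. The covariates are given as examples, and the risk factors are introduced as what the set includes. A reader might infer that the plan excludes body size from adjustment. The text does not support that: it fails to name BMI and fixes no covariate set. The Discussion also promises a broad look at physiological factors affecting response, which could take in body size.

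**A journal article need not carry a full covariate list.** This is fair, and it is why the point is not an error. What the article does state is that adjustment is conditional on an undefined need, and that is worth tightening.

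**The article does not say that body size affects 25(OH)D.** Correct. A reader might infer that BMI is an established confounder in this trial. The article supports only plausibility, through the fixed dose. Its links to activity, diet, glycaemic control or T-score are likewise not documented there.

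**Confounding does not reach the arm comparison, and the gain there is small.** Both are correct. A reader might infer that the primary comparison is biased or underpowered for lack of BMI; neither follows.

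**It may be too late to pre-specify.** Recruitment ran to December 2013 and visits to June 2014, and the analysis is written in the past tense, although the Discussion calls analysis ongoing. This bears on how the adjusted result is labelled, not on whether it is useful.

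**Conclusion.** The point holds as a minor improvement. Baseline weight and BMI are collected and dosing is fixed in IU, yet neither variable is named in the risk-factor list or among the example covariates, and the rule for adjusting has no criterion.

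The randomised comparison remains unbiased. It gives up about 2% to 8% in standard error, which rests on the assumed correlation of 0.2 to 0.4. The half-widths and power figures also assume an SD of 25 nmol/L and 51 evaluable patients per arm. No figure in the article changes.

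The greater value lies in the observational risk-factor models, where a body-size effect, if there is one, could be read as an effect of activity, diet or glycaemic control. The size of that misattribution cannot be estimated from the document.

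**What to change.** 1. In the 25(OH)D analysis, include baseline BMI (or weight; choose one) as a fixed continuous covariate, in place of adjustment decided case by case.
2. Add the same variable to the candidate list for both the vitamin D and the bone-health risk models.
3. If outcome data have already been seen, keep the planned analysis as it stands and report the BMI-adjusted one as a sensitivity analysis, labelled as such.

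The cost is one degree of freedom per model and a sentence or two of text. No new data are needed, and the sample size is unaffected.
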